## Abstract

**Background:**

International guidelines recommend structured diabetes education to empower individuals with type 2 diabetes (T2D). While DESMOND is an effective programme for T2D management, it is often inaccessible to people with intellectual disabilities (ID) due to their unique needs. There is limited evidence on the effectiveness of adapted T2D education for this group, despite the importance of tailored support in preventing complications and early mortality.

We previously adapted the DESMOND programme for adults with ID, creating DESMOND-ID. A feasibility study showed it is possible to recruit and deliver the programme to adults with ID and their carers, who found it valuable. Initial findings suggest DESMOND-ID may improve blood glucose control, warranting further investigation through a large-scale randomised controlled trial (RCT).

**Methods:**

The "My Diabetes & Me" study will be conducted in two stages: an internal pilot and a main RCT. The pilot will recruit 108 participants over 10 months to assess recruitment and retention, using glycated haemoglobin (HbA1c, mmol/mol) at six months as the primary outcome. This will inform the design of the main study.

Across both stages, 450 participants will be randomly assigned to receive either the DESMOND-ID intervention or treatment as usual (TAU). The intervention group, with their carers, will attend weekly sessions for seven weeks, plus two booster sessions at one and three months post-programme.

Primary outcome is HbA1c at six months. Secondary outcomes include HbA1c at 12 and 18 months (pilot only), anthropometric data, self-reported outcomes, and other risk factors. A process evaluation will explore barriers and facilitators to implementation using qualitative and quantitative methods.

**Conclusion:**

DESMOND-ID is the first structured T2D education programme tailored for adults with ID, and this RCT is the first to evaluate its clinical and cost-effectiveness.

**Trial Registration:**

09/11/2022

ISRCTN83150600 (
https://doi.org/10.1186/ISRCTN83150600)

## Background

Worldwide the International Diabetes Federation (IDF) estimates that 589 million people have diabetes and more than 90% of these people have type 2 diabetes (T2D)
^
1
^. According to the World Health Organisation (WHO), T2D is increasing in the general population, bringing significant health risks, and rising costs for healthcare providers globally
^
2
^. According to the National Institute for Health and Care Excellence [NICE], management of T2D aims to optimise blood glucose levels (HbA1c) to avoid long-term complications (e.g. retinopathy, foot problems, kidney disease, peripheral and autonomic neuropathy, and cardiovascular disease) and earlier and avoidable death
^
3
^. Individuals living with T2D require considerable self-care skills and practices to self-manage their condition, and avoid negative health behaviours in relation to diet, physical activity, BMI, blood pressure, smoking, alcohol consumption, and medication adherence
^
3
^. However, some find this difficult and diabetes self-management education (DSME) programme
^
4
^.

DSME programmes can help improve self-care behaviours, quality of life, lower HbA1c levels and impact disease progression
^
5
^. Diabetes education has been shown to be cost-effective by reducing hospital admissions and lowering lifetime healthcare costs through a reduced risk of complications
^
6,
7
^. Within the UK, the National Service Framework for Diabetes: Standards
^
8
^, the NICE guidelines on T2D
^
3
^ and the UK’s Department of Health guidance
^
9
^, all recommended that everyone with T2D should be offered the opportunity to attend a DSME programme. The most established and robustly evaluated, DSME programme implemented across the UK is DESMOND
^
10
^.

DESMOND (Diabetes Education and Self-Management for Ongoing and Newly Diagnosed) is a 6-hour group education programme, delivered by health professionals and lay educators over two half days or one full day. DESMOND (and similar DSME programmes) have been found to improve individuals’ understanding of T2D, improve diet, increase physical activity, reduce weight, help effective smoking cessation; reduce depression, and promote positive behaviour change, thereby improving cardiovascular disease risk factors (blood pressure, blood lipids, cholesterol) and decreasing glycated haemoglobin (HbA1c) levels, with sustained improvements maintained at 12-months and three years
^
10–
13
^. DESMOND is a is a cost-effective educational intervention in the management of T2D
^
6,
14
^.

Since the original DESMOND initiative for people diagnosed with T2D, it has been successfully adapted to meet the needs of underserved populations and those who are at increased risk of T2D, including those from ethnic minority communities
^
15,
16
^, people with T2D and co-morbidities
^
17
^, those at risk of diabetes
^
18
^, and women with gestational diabetes
^
19
^. A fundamental goal of DESMOND is a more engaged and empowered individual, whereby the person living with diabetes becomes the expert. The robust evidence of the clinical and cost-effectiveness of the DESMOND education programmes have strongly highlighted the importance of structured group education to support T2D self-management systematically. The roll-out of DESMOND across the UK has enabled healthcare providers to meet many of the demands of people with T2D, but it had not been offered to, or adapted for, people with ID
^
20–
22
^ before our earlier work
^
23
^.

The American Association for Intellectual and Developmental Disabilities define an ID as:

*‘A disability characterised by significant limitations in both intellectual functioning and adaptive behaviour as expressed in conceptual, social, and practical skills. This disability originates during the developmental period, which is defined operationally as before the individual attains age 22.’*
^
24
^

Intellectual functioning relates to intelligence, alongside the belief that it is influenced by human functioning dimensions and systems of support
^
24
^. Whilst adaptive behaviour includes conceptual skills (e.g., language and literacy, self-direction), social skills (e.g., interpersonal skills, ability to follow rules) and practical skills (e.g., personal care, use of money/phone) that have been learned and are performed by individuals in their daily lives
^
25
^. To explain the wide range of different abilities the idea of a continuum of disability has been used from mild, moderate, severe and profound ID.

Within the UK approximately 1.3 million adults (18+ years) are said to have an ID
^
26
^. People with ID are now living longer and developing more chronic physical health conditions such as diabetes
^
27
^. T2D is 2–3 times more common in people with ID than the general population
^
20,
21
^, and this population have poorer outcomes including delayed diagnosis, poor management of symptoms, more severe complications, unnecessary hospitalisations, and premature mortality. Furthermore, they are not offered the DSME programmes recommended for, and routinely available to the general adult population
^
20–
22
^.

The Equality Act 2010
^
28
^ in the UK sets out the legal requirement for public health services to provide reasonable adjustments for people with a disability, which should include provision of accessible therapeutic and educational support. Addressing this gap is a UK NHS priority to avoid premature deaths and serious diabetic complications, to improve healthcare among people with ID and to reduce costs for healthcare providers. Yet if people with ID and T2D are not offered diabetes education programmes, they cannot benefit from the potential health improvements that have been found for other populations.

Current national UK diabetes education programmes, and other structured diabetes education programmes internationally, have not been tailored to address the needs of people with ID, which include their cognitive and communication needs, low literacy skills and learning styles
^
20–
22
^. This is despite the UK’s NICE guidelines for T2D management
^
3
^ recommending that diabetes education should meet the specific needs of different populations. Evidence of the impact of structured diabetes education programmes targeting HbA1c for adults with ID is sparse. We aim to fill this gap by evaluating a structured T2D education programme for adults with ID and to determine if it is clinically and cost-effective compared to TAU.

During our recent Diabetes UK feasibility study
^
23
^, we successfully adapted and tested DESMOND for use with adults with ID (creating the DESMOND-ID programme). DESMOND-ID is delivered over 7 weeks (2 hours per week), where the adult with ID is accompanied by a family/paid carer or spouse/partner or supporter, where available, followed by two booster sessions at one and three months later. Our feasibility study has also shown that DESMOND-ID can be delivered to adults with ID and T2D in the context of a randomised trial
^
23
^. In addition, it is possible to identify and recruit adults with ID and T2D into such a study, obtain informed consent, obtain blood samples, administer questionnaires, and randomise the adults to either the intervention or TAU. The feasibility study suggests that DESMOND-ID may be able to decrease HbA1c levels. In addition, DESMOND-ID was valued and accepted by adults with ID, carers and educators. Results were promising but need confirming in a definitive randomised trial.

Therefore, the aim of this prospective study is to determine whether DESMOND-ID is effective towards management of HbA1c and cost-effective compared to TAU in adults with ID and T2D. We will test if DESMOND-ID can bring about the same benefits for adults with ID as the DESMOND studies have shown for adults in the general population, improving the health of people living with T2D and ID, and reducing inequalities in health.

## Objectives

1.To conduct a UK-wide, multicentre randomised trial to determine the effectiveness of DESMOND-ID on improving HbA1c levels (primary outcome) and a range of secondary outcomes compared to TAU.2.To determine the cost-effectiveness of DESMOND-ID compared to TAU via a within-trial economic evaluation and a long-term model.3.To determine the facilitators, barriers and mechanisms of actions involved in the DESMOND-ID process via a process evaluation.

## Methods and design

### Patient and Public Involvement (PPI)

Our PPI partners for this study are Compass Advocacy Network (CAN) a non-profit organisation in Northern Ireland who work with work with children and adults with learning disabilities, autism and mental health issues. Staff and service users at CAN have been involved with the DESMOND-ID programme since our original feasibility testing phase in 2018
^
23
^. Feedback obtained from our PPI partners during this phase enabled us to refine the DESMOND-ID content and delivery based upon the unique healthcare challenges experienced by adults with learning disabilities, prior to the commencement of our RCT.

In preparation for this RCT our PPI partners at CAN helped us to develop and test user-friendly participant information sheets adapted to meet the comprehension and communication needs of adults with learning disabilities. In addition, they led on the development of a suite of promotional materials, such as videos and posters, to help support participant recruitment.

We will work with our PPI partners throughout the study to develop a suitable dissemination plan, ensuring findings from our study reach a wide ranging audience. We will work with our PPI partners to refine the data to ensure that the results are formatted and presented in a manner that is suitable for adults with learning disabilities and their advocates.

### Study design

The My Diabetes and Me study is a 2-stage parallel group randomised trial with an internal pilot, economic evaluation and process evaluation. The internal pilot (Stage 1) will run for 10 months to assess recruitment rates and retention for the primary outcome at 6 months. The internal pilot will also allow us to identify any key difficulties and address them in preparation for the main study. The first three clinical sites will recruit a total of 108 adults with ID and T2D during this period. Participants enrolled in the pilot will be included in the analysis of the main study. We will use Avery
*et al.,*
^
29
^ traffic light system to guide our progression criteria as recommended in recent best practice. This protocol is reported in accordance with the Standard Protocol Items: Recommendations for Interventional Trials (SPIRIT) guidelines
^
30
^.

### Study sample

In total, 191 participants in each randomised group will have 90% power to detect a difference in means of 0.5% in HbA1c (mmol/mol) at 6 months. This 0.5% cut-off point is accepted in the diabetes community as being a minimal clinically important difference, ensuring that an effect of this size or greater will be seen as a meaningful indication of the effectiveness of the intervention
^
5
^. We assumed a standard deviation of 1.5%
^
31
^ and used a two-group t-test with a 0.05 two-sided significance level. Assuming a dropout rate of 15%, the sample size required is 450 participants (225 per group). This dropout rate is likely to be an overestimate because our feasibility study showed that <10% of recruited adults with ID dropped out
^
23
^ and other National Institute for Health and Care Research (NIHR) ID intervention studies have reported similar results
^
32,
33
^.

The current intention is to seek an excess of 30%–40% individuals within the ID and T2D population over this sample size who might be willing to take part in the study. Therefore, 585–630 adults with ID and T2D will be identified to provide some flexibility for those not meeting the criterion, refusals and dropouts. This 30%–40% is a generous estimate and is based on our feasibility study’s recruitment rates
^
23
^ and other diabetes and ID studies
^
34
^.

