### Randomisation and treatment allocation

When informed consent has been obtained participants will be randomised by the Northern Ireland Clinical Trials Unit (NICTU) using a centralised randomisation system in a 1:1 ratio, with allocation concealed until the person joins the study. Randomisation will be completed by an appropriately trained and delegated member of the NICTU team. Participants will be allocated to the intervention or TAU group. Randomisation will be stratified by site. At the time of randomisation, each participant will be allocated a unique alphanumeric code which will be used throughout the study for participant identification. The research team will then ensure that the participant’s GP is informed of their participation in the study. Due to the nature of the intervention, it is not possible to blind participants to their allocated treatment.

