### Study intervention

DESMOND/DESMOND-ID is based on a series of psychological theories of learning and education: Leventhal’s Common-Sense Theory (i.e. illness representation, illness beliefs
^
36
^), Dual Process Theory (process of learning
^
37
^), and Social Learning Theory (i.e. self-efficacy
^
38
^). The philosophy of the programme was founded on the empowerment of individuals living with diabetes, as evidenced in published work
^
39
^ and its development followed a systematic approach, guided by the MRC framework for developing and evaluating complex interventions
^
40,
41
^.

In My Diabetes and Me, the DESMOND-ID programme will be delivered face-to-face in a range of community settings over a period of 7 weeks to 6–8 adults with ID and T2D and their carer/partner/advocate in a group setting, with two booster sessions in subsequent months (1 and 3 months after the end of the weekly sessions). The education sessions will be delivered by two healthcare professionals in each site, who will receive 3 days of training in DESMOND-ID education programme, plus an additional day of training before delivery of the booster sessions. The healthcare professionals will also be allocated 3 days for preparation and supervision of the delivery of the intervention. Staff from the DESMOND-ID team will conduct several quality assurance checks at each site throughout the duration of delivery.

Week 1 of the programme focuses on carers/partners/advocates only with the aim of improving their understanding of T2D and how DESMOND-ID works along with their supporting role. In weeks 2–7, we encourage the adult with ID/T2D and their carer/partner/advocate to attend together if possible. These weeks focus on: introductions to ‘My story with T2D, My body and T2D; What is T2D; What does T2D do to your body; Food and blood sugar, Knowing what your blood sugar levels mean; Being active; Heart and circulation problems; Other T2D health problems; What can I do to keep healthy; Food and fats; Making healthier food choices; and Developing a diabetes health action plan’ (see
Table 1).

**Table 1. T1:** DESMOND-ID structured education programme session plan.

Week 1	Week 2	Week 3	Week 4	Week 5	Week 6	Week 7
Carers and advocates only session.	Welcome and introduction (25 mins)	Welcome back (20 mins)	Welcome back (20 mins)	Welcome back (20 mins)	Welcome back (20 mins)	Welcome back (20 mins)

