### Data analysis

The primary analysis will be conducted on all outcome data obtained from all participants as randomised and regardless of protocol adherence, i.e. intention to treat analysis according to their randomisation group. Per protocol analysis will also be carried out: patients who attended all 6 education programme sessions and at least one booster session. A detailed statistical analysis plan (SAP) will be developed. Baseline characteristics and follow-up measurements will be summarized as means and standard deviations, medians and inter-quartile ranges, or numbers and percentages, as appropriate. The difference between randomised groups in change from baseline at 6-months for HbA1c (mmol/mol) levels will be analysed using a t-test. Analysis will use a significance threshold of
*p* ≤ 0.05. Secondary analysis for the primary outcome using ANCOVA will adjust for baseline and site. The comparison of other continuous outcomes between the two groups will be investigated using analysis of covariance, adjusting for baseline/other covariates where appropriate or t-test. Dichotomous outcomes will be analysed using chi-square and logistic regression if adjustment for covariates is required. Any adjustment for covariates will be based on clinical input and pre-specified in the SAP. To ensure the quality of the data and trial, we have established a trial steering committee and an independent Data Monitoring Committee which consists of experts external to the trial.

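### DESMOND-ID is taught in groups in one arm only, but the sample size and primary t-test assume independent participants; with any positive within-group correlation the stated 90% power is too high and the standard error leaves out a variance component

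*Protocol article*

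**What the plan says.** Participants are randomised individually, "using a centralised randomisation system in a 1:1 ratio", stratified by site (Randomisation and treatment allocation). The programme is then delivered "to 6–8 adults with ID and T2D and their carer/partner/advocate in a group setting" over seven weeks, followed by two booster sessions (Study intervention). On staffing: "The education sessions will be delivered by two healthcare professionals in each site". Controls receive usual care and a book, with no group education (Treatment as usual group).

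The Study sample section states that "191 participants in each randomised group will have 90% power to detect a difference in means of 0.5% in HbA1c (mmol/mol) at 6 months". It adds "We assumed a standard deviation of 1.5"%, "and used a two-group t-test with a 0.05 two-sided significance level", and then "Assuming a dropout rate of 15%, the sample size required is 450 participants (225 per group").

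The Data analysis section says: "The difference between randomised groups in change from baseline at 6-months for HbA1c (mmol/mol) levels will be analysed using a t-test". The only other model it names for the primary outcome is an ANCOVA adjusting for baseline and site. The article gives no ICC, no design effect and no term for teaching group or educator.

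**The concern.** People who share a teaching group share educators, peers and sessions. The programme's stated theoretical basis includes social learning, so an ICC of exactly zero is hard to defend. Any such correlation exists in the intervention arm only.

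Both the power calculation and the two-sample t-test take the variance of the intervention mean as if all participants were independent. The between-group component is left out. At stake are the accuracy of the 90% power claim, the width of the confidence interval for the primary effect, and whether the test keeps its 5% level. Adjusting for site does not help, because teaching groups vary within site and in one arm only.

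**Working it through.** **Inputs from the protocol.** Difference 0.5, SD 1.5 (same scale, so only their ratio matters), two-sided 5%, 191 analysed per arm, 15% dropout, 225 randomised per arm, groups of 6–8 taught.

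**Inputs assumed.** ICC 0.01–0.10, and total variance 1.5² in both arms.

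**1. Reproduce the stated figures.** The exact t-test (noncentral t) gives power 0.8999 at 190 per arm and 0.9013 at 191, so 191 is right. 191 / 0.85 = 224.7, which rounds up to 225 per arm and 450 in total. Both figures match under independence, so no allowance for clustering is hidden in them.

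**2. Group size at analysis.** Groups of 6–8 are people taught, whereas 191 is the number left after dropout. A group of 7 leaves 7 × 0.85 = 5.95 analysed, so m = 6 is used. Pairing full groups of 7 with 191 analysed would overstate the effect.

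**3. Clustering in one arm.**
- Design effect in the intervention arm: DE = 1 + (m − 1) × ICC
- SE = 1.5 × √((DE + 1) / 191)
- Power of a correctly sized test = Φ(0.5 / SE − 1.96)
- Type I error of the unadjusted t-test = 2 × [1 − Φ(1.96 / √((DE + 1) / 2))]

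Example at ICC 0.05: DE = 1.25; SE = 1.5 × √(2.25 / 191) = 0.1628; 0.5 / 0.1628 = 3.071; power = Φ(1.111) = 86.7%. For type I error, 1.96 / √1.125 = 1.848, giving 6.5%.

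| ICC (assumed) | DE | SE | Power, normal | Power, t with Satterthwaite df | Type I error, unadjusted t-test |
|---|---|---|---|---|---|
| 0 | 1.00 | 0.1535 | 90.3% | 90.1% (exact t-test) | 5.0% |
| 0.01 | 1.05 | 0.1554 | 89.6% | 89.0% | 5.3% |
| 0.02 | 1.10 | 0.1573 | 88.9% | 88.3% | 5.6% |
| 0.05 | 1.25 | 0.1628 | 86.7% | 86.0% | 6.5% |
| 0.10 | 1.50 | 0.1716 | 83.0% | 82.1% | 8.0% |

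Taught groups of 6 to 8 leave 5.1 to 6.8 analysed. At ICC 0.05 that gives power of 87.3% to 86.1% and type I error of 6.2% to 6.7%.

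**4. Offset from site stratification.** Randomisation is balanced by site but the t-test ignores site, so its estimated variance includes site differences that do not affect the comparison. With 5% of variance between sites (assumed), the ratio of true to estimated variance is about 0.95 + 2.5 × ICC, that is 0.975 / 1.00 / 1.075 / 1.20. Type I error is then about 4.7% / 5.0% / 5.9% / 7.4%. A simulation gave 4.9% / 5.2% / 6.0% / 7.7%.

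**5. Does adjusting for site cure it?** No. In a simulation of 8 sites with 4 groups of 6, at ICC 0.05 and a site share of 0–5%, the t-test rejected 6.1–6.4% of true nulls and the site-adjusted model 6.4–6.7%.

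**6. Lower dropout.** At 10% dropout, 225 × 0.9 gives about 202 per arm and 7 × 0.9 = 6.3 per group. Power is then about 91% / 90% / 88% / 85%. Type I error does not improve.

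**7. Baseline adjustment, shown separately.** Suppose the SD of 1.5 is cross-sectional and the correlation between baseline and six months is 0.5 (both assumed). The residual SD is 1.5 × √(1 − 0.25) = 1.299. With no clustering, power at 191 per arm is Φ(0.5 / (1.299 × √(2 / 191)) − 1.96) = 96.4%. With DE as in the table it is 96.0% / 95.6% / 94.4% / 92.0%. Power above 90% here comes from the covariate, not from modelling the groups.

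**The case against.** The strongest objection is that the size rests on a figure the protocol does not contain. HbA1c is a laboratory measure, and nothing in the article shows that it clusters strongly in short education groups. At ICC 0.01–0.02 power falls by less than two points. The Study sample section also expects dropout below 15%, and at 10% that restores power to about 90–91% at those values. All of this stands.

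A reader might infer that the planned t-test is anti-conservative whatever the ICC. The documents do not support that: randomisation is stratified by site, the t-test ignores site, and at low ICC the two effects roughly cancel. A reader might also infer that the trial is too small. That does not follow either, because the shortfall is modest over most of the range and an analysis using baseline could recover it.

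It can also be said that the promised statistical analysis plan may handle clustering. It may well add a sensitivity analysis. But the protocol itself fixes the primary test and the power statement, and its provision for adjustment concerns covariates, not a random group effect.

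On the other side, two educators per site may teach successive groups, so effective clusters could be larger than a single group. This is not included in the table.

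**Conclusion.** The point holds in conditional form. For any positive within-group ICC, the 90% power at 191 per arm is overstated and the standard error of the primary comparison omits the between-group component. Over an assumed ICC of 0.01–0.10 with about 6 analysed per group, power is about 89.6% down to 83.0%, and the unadjusted t-test's type I error is about 5.3% up to 8.0%. With 5% of variance between sites, type I error is about nominal at ICC 0.01–0.02, about 6.0% at 0.05 and about 7.7% at 0.10. The type I figures assume group-level variation around a zero average effect.

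The direction of the power loss and of the missing variance is certain once the ICC is positive; the size is not. This should be fixed because it concerns the primary inference and costs little. The documents do not show that the primary result would be invalid.

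**What to change.** - Record the DESMOND-ID group identifier for each intervention participant. Attendance lists are already study records (process evaluation, Table 2). The analysis plan should also say how participants who never attend are coded.
- Make the primary analysis a partially nested linear mixed model: a random group effect in the intervention arm only, usual-care participants as singletons, small-sample degrees of freedom, and adjustment for baseline HbA1c and site.
- Restate power in the Study sample section over a stated ICC range and analysed group size. Show any gain from baseline adjustment on its own line, with its assumed correlation.

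No extra patients are needed. The cost is a wording change in the protocol and analysis plan, one data field, a slightly wider confidence interval than the same analysis without the group effect, and a less favourable power figure before baseline adjustment.
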